### Parent rated measure

**Parents’ perceived ability to cope with children’s negative emotions** will be measured using the Coping with Children’s Negative Emotions Scale – Adolescent Version (CCNES-A).^35^ This scale assesses parents’ perceived ability to respond to their children’s negative emotions across six subscales: emotion-focused, problem-focused, minimization, punitive, expressive encouragement, and distress responses. Each subscale includes 9 items, rated on a 7-point scale, with higher scores indicating greater use of that particular coping style, except for the expressive encouragement subscale which is reverse-scored.

**Parents’ perception of adolescents’ behavioral emotion regulation** will be measured using the Behavioral Emotion Regulation Questionnaire (BERQ).^36^ This scale assesses parents’ perceptions of their adolescent’s use of behavioral emotion regulation strategies across five subscales. Each subscale includes 4 items, yielding a total subscale score ranging from 4 to 20, with higher scores indicating greater use of that specific strategy.

**Healthcare and other societal resource use** for both children and caregivers will be reported by parents using the Trimbos/iMTA Questionnaire for Costs associated with Psychiatric Illness (TiC-P).^37^ This instrument assesses healthcare utilization and other societal resource use related to psychiatric illness.

**Demographic background data:** Parents will answer questions about the parental educational level, occupational status, prior treatment history, and information on how the participants got in contact with the study will be registered (e.g., via self-referral or referral from health care).

**Study-specific parental reports** will be used to assess any changes in the child’s psychotropic medication since the end of the POET treatment, including dosage adjustments, discontinuation, or initiation of new medications.

### Adolescent, parent, and clinician measures:

**Credibility and expectancy** will be measured using The Credibility/Expectancy Questionnaire (CEQ).^38^ The scale consists of 6 items which are rated on a 9-point scale (1 = not at all to 9 = very much), except for items 4 and 6, which are rated from 0% to 100%. Higher scores indicate greater perceived credibility and expectancy. The questionnaire is clinician-, adolescent-, and caregiver-reported. Adolescents and parents will complete the full CEQ before treatment and after the first treatment module. Thereafter, one selected CEQ item will be administered weekly to monitor changes in credibility and expectancy over time. Clinicians will complete the CEQ before treatment and after half of the treatment has been completed.

**Client satisfaction is measured using** The Client Satisfaction Questionnaire (CSQ)^39^ will be used to assess satisfaction with treatment. The scale consists of 8 items, yielding a total score ranging from 8 to 32, with higher scores indicating greater treatment satisfaction. The questionnaire is self-rated immediately after treatment by adolescents and caregiver reported.

### Distal outcomes

**Information on other distal outcomes** will be collected through linkage with Swedish national registries. Data will include academic performance (grade point average and eligibility for further education), occupation (employment status, sick leave, and highest level of education), psychopharmacological treatment (prescription and use of medication for psychiatric symptoms), and health care utilization (diagnoses, type of care, and occurrences of self-harm. The relevant registers and the types of data to be collected are presented in the table below.

# Table 1. Relevant registers and the types of data to be collected for analyses of distal outcomes

| **Register** | **Data of interest** |
| --- | --- |
| National Patient Register | Diagnosis, healthcare utilization, type of care, and suicide attempts |
| VAL Database | Diagnosis, healthcare utilization, type of care, and suicide attempts |
| Prescribed Drug Register | Prescription and consumption of medication for psychiatric symptoms |
| LISA (Longitudinal Integration Database for Health Insurance and Labour Market Studies) | Employment status, sick leave, and highest educational level |
| Swedish National Agency for Education: Quality Declaration, Compulsory School (final grades) | Grades and eligibility |
| Swedish National Agency for Education: Quality Declaration, Upper Secondary School (grade records) | Grades and eligibility |

# Table 2. Information on the time points for completion and responders of measurements related to all hypotheses

|  | TRIAL PERIOD | | | | | | | | | | | | |
| --- | --- | --- | --- | --- | --- | --- | --- | --- | --- | --- | --- | --- | --- |
|  | Enrolment | Randomization | Post-randomization | | | | | | | | | | |
| Assessment point | Baseline | | 1w | 2w | 3w | 4w | 5w | 6w | POST | 3M | 12M | | 60M |
| **ENROLMENT** |  | |  |  |  |  |  |  |  |  |  | |  |
| Eligibility screen | X | |  |  |  |  |  |  |  |  |  | |  |
| Informed consent | X | |  |  |  |  |  |  |  |  |  | |  |
| Randomization | X | |  |  |  |  |  |  |  |  |  | |  |
| **TREATMENT**  POET  Supportive treatment |  | |  | | | | | |  | | | | |
| **ASSESSMENTS** |  | |  |  |  |  |  |  |  |  | |  |  |
| ***Clinician rated*** |  | |  |  |  |  |  |  |  |  | |  |  |
| MINI-KID | X | |  |  |  |  |  |  |  |  | |  |  |
| CGI-S | X | |  |  |  |  |  |  | X | X | | X | X |
| CGI-I |  | |  |  |  |  |  |  | X | X | | X | X |
| C-GAS | X | |  |  |  |  |  |  | X | X | | X | X |
| WSAS | X | |  |  |  |  |  |  | X | X | | X | X |
| RCADS-47 | X | |  |  |  |  |  |  | X | X | | X | X |
| CEQ | X | |  |  | X |  |  |  |  |  | |  |  |
| PIAS |  | |  |  | X |  |  |  | X |  | |  |  |
| ***Adolescent rated*** |  | |  |  |  |  |  |  |  |  | |  |  |
| RCADS-11 | X | | X | X | X | X | X | X | X | X | | X | X |
| PMERQ-short | X | |  |  |  |  |  |  | X | X | | X | X |
| Selected items from PMERQ-short |  | | X | X | X | X | X | X |  |  | |  |  |
| DERS-16 | X | |  |  |  |  |  |  | X | X | | X | X |
| Selected items from DERS-16 |  | | X | X | X | X | X | X |  |  | |  |  |
| ERQ-CA | X | |  |  |  |  |  |  | X | X | | X | X |
| Selected items from ERQ-CA |  | | X | X | X | X | X | X |  |  | |  |  |
| PAQ-S | X | |  |  |  |  |  |  |  | X | | X | X |
| DSHI-Y |  | |  |  |  |  |  |  | X | X | | X | X |
| PANAS | X | | X | X | X | X | X | X | X | X | | X | X |
| SEQ-C | X | | X | X | X | X | X | X | X | X | | X | X |
| BSL-23 | X | |  |  |  |  |  |  | X | X | | X | X |
| EBQ | X | |  |  |  |  |  |  | X | X | | X | X |
| CHU-9D | X | |  |  |  |  |  |  | X | X | | X | X |
| CSQ |  | |  |  |  |  |  |  | X |  | |  |  |
| Study specific questionnaire on Adverse events |  | |  |  |  |  |  |  | X |  | |  |  |
| CEQ | X | |  |  |  |  |  |  |  |  | |  |  |
| One selected item from CEQ |  | | X | X | X | X | X | X |  |  | |  |  |
| Single-item assessment of suicidal ideation and plans | X | | X | X | X | X | X | X | X | X | | X | X |
| CSQ |  | |  |  |  |  |  |  | X |  | |  |  |
| ***Parent rated*** |  | |  |  |  |  |  |  |  |  | |  |  |
| RCADS-47 | X | |  |  |  |  |  |  |  | X | | X | X |
| DERS-16 | X | |  |  |  |  |  |  |  | X | | X | X |
| CCNES-A | X | |  |  |  |  |  |  |  | X | | X | X |
| BERQ | X | |  |  |  |  |  |  |  | X | | X | X |
| TIC -P | X | |  |  |  |  |  |  |  | X | | X | X |
| CEQ | X | |  |  |  |  |  |  |  |  | |  |  |
| One selected item from CEQ |  | |  | X | X | X | X | X |  |  | |  |  |
| CSQ |  | |  |  |  |  |  |  |  | X | |  |  |

Abbreviations: 1w, 1 week; 2w, 2 week; 3w, 3 week; 4w, 4 week; 5w, 5 week; 6w, 6 week, POST, Immediately after treatment; 3M, 3 months after treatment; POET, Primary Care Online Emotion Regulation Treatment; MINI-KID,The Mini-International Neuropsychiatric Interview for Children and Adolescents; CGI-S, The Clinical Global Impressions-Severity; CGI-I, The Clinical Global Impressions-Severity; C-GAS, Children’s Global Assessment Scale; WSAS, The Work and Social Adjustment Scale; RCADS-47, The Revised Child Anxiety and Depression Scale; CEQ, The Credibility/Expectancy Questionnaire; PIAS, Internet Cognitive Behavior Therapy Adherence Scale; RCADS-11, The Brief Revised Child Anxiety and Depression Scale for Adolescents; PMERQ, The Process Model of Emotion Regulation Questionnaire – Short; DERS-16, The Difficulties in Emotion Regulation Scale - 16-item version; ERQ-CA, The Emotion Regulation Questionnaire for Children and Adolescents; PAQ-S,The Perth Alexithymia Questionnaire-Short Form; DSHI-Y, Deliberate Self-Harm Inventory Youth version; PANAS, Positive and Negative Affect Schedule for Children; SEQ-C,The Social Self-Efficacy subscale of Self-Efficacy Questionnaire; BSL-23, Borderline Symptoms List Supplement; EBQ, The Emotion Beliefs Questionnaire; CHU-9D, The Child Health Utility 9D; CSQ, The Client Satisfaction Questionnaire, CCNES-A, The Coping with Children’s Negative Emotions Scale - Adolescent Version; BERQ, The Behavioral Emotion Regulation Questionnaire; TIC-P, Trimbos Questionnaire for Costs associated with Psychiatric Illness.

## Reimbursement

Adolescents will be compensated with a gift card worth 100 SEK for each completed assessment after the treatment period (up to a maximum total of 800 SEK).

## Inter-Rater Agreement

Through-out the trial therapist and blind assessors attend regularly workshops in which we conduct inter rater agreement of audio recorded blind assessment interviews. To evaluate inter-rater reliability, 10% of all baseline assessment and blinded assessment ratings will be independently rated by an assessor. The additional rating will be used to estimate the level of agreement between evaluators and to ensure consistency and reliability in clinical assessments across raters. Before conducting assessments all therapist and blind assessors had to conduct inter- rater agreement introduction consisting of several inter-rater agreement ratings. Therapists and blind assessors could not begin conducting ratings until inter-rater agreement had been reached with the other assessors.

# Methods: Assignment of interventions

## Randomization

Eligible participants will be randomly assigned (1:1) to either the POET intervention or the Supportive Treatment condition. Randomization will be conducted in blocks of four or six within each participating Region. An independent researcher, not involved in participant recruitment or treatment delivery, will perform the randomization using an online system (Sealed Envelope Ltd) that employs a secure pseudo-random number generator.

## Blinding

Primary and secondary clinician outcome measures will be assessed by a clinician blind to treatment allocation before treatment (before randomization), immediately after treatment, and 3 months after treatment, and at 1 and 5 years follow up. To ensure the integrity of blinding procedures, participants will be provided with explicit instructions not to reveal their treatment allocation to the blind rater. After completing the assessment, the blind raters guess the participant’s group allocation and disclose the reason for their guess (e.g., true random guess) and report any disclosed group allocation. We will examine whether blinded assessors’ treatment allocation guesses differ from chance. Blind assessments will be audio-recorded to allow for calculation of inter-rater reliability. The participants, therapists, and the project manager are not blind to treatment allocation. Blinded assessors will receive thorough training in the clinician-rated measures and must demonstrate adequate inter-rater agreement before conducting blinded assessments.

## Data management

Subjects who participate in the trial are coded with a trial-specific identification code. All subjects are registered in a subject identification code list that connects the subject’s name and personal number with a subject number/trial identification number. The code key is stored in a security-classified database for sensitive personal data within the organization of the sponsor. Data is stored in accordance with the sponsors archival rules for research documents.

All individuals handling personal data are bound by confidentiality agreements and/or professional secrecy obligations through their employment terms or confidentiality agreements in accordance with the sponsor.

All correspondence between participants and therapists will take place on platforms which require two-factor authentication.

Assessments are administered via the internet and all answers, from participants and clinicians, are securely stored on a database developed for this purpose and have been used in several completed and ongoing studies. All data traffic is encrypted, ensuring a high security level.

### Archiving

Data is archived in accordance with the sponsors archival rules for research documents

### Interim analysis

No interim analysis will be conducted.

## Statistical methods

### Power analysis

#### Primary outcome

A simulation-based power analysis was performed. Based on the data from the pilot study)^15^, a simpler model without random effects was fitted to estimate the effect of time and the thresholds. Data was then generated using these values, and parameters that were varied, namely sample size, interaction between time and treatment (log-odds), and the variance of the random effect. Sample size took the values of 250, 300, 350, and 400, the interaction effect took the values of 0.59, 0.69, 0.79, and 0.88 (corresponding to ORs of 1.8, 2.0, 2.2, and 2.4), and the variance of the random effect took the values of 1.48 and 2.22 (corresponding to ICC of 0.4 and 0.6). For each combination of parameters, 700 datasets were simulated, and a cumulative link mixed model (CLMM) was fitted to the data. The p-value of the interaction effect was saved for each simulation, and power was calculated as the proportion of p-values less than 0.05. The CLMM model fitted in each iteration included a random intercept for participant, a dummy-coded time variable (before treatment, after treatment), the treatment condition, and the interaction between the time variable and treatment. The results from the power analysis are shown in Figure 2.

We concluded that 350 participants would give us >80% power to detect an interaction between treatment and time with an OR of 2.2. To allow for ~10% attrition, we set N to 388 participants.

# Figure 2. visualization of power analysis results for primary outcome

[figure not shown]

#### Secondary continuous outcomes

A simulation-based power analysis was performed using a linear mixed-effects model. Assuming two time points (before treatment and immediately after treatment), 388 participants (194 per group), 10% attrition, ICC = 0.5, and a two-sided test at α = 0.05, the study has >80% power to detect a difference 0.30 (Cohen’s d) between groups immediately after treatment.

### Analysis population

Analyses will be conducted according to the intention-to-treat (ITT) principle.

### Inter-rater reliability of primary outcome

To assess inter-rater reliability, Krippendorff’s alpha will be calculated, as it is suitable for nominal and ordinal data and allows for different raters to have evaluated different subsets of cases.^40^

### Analysis of Baseline Characteristics

Demographic and baseline characteristics will be summarized for each treatment group. In accordance with CONSORT 2025 recommendations, no significance testing of baseline differences will be performed.^41^ Data distributions and potential outliers will be visually inspected, and sensitivity analyses will be run without outliers. Categorical variables will be summarized as counts and percentages; ordinal and continuous variables as medians and interquartile ranges or means and standard deviations, as appropriate. Data will be analyzed according to the participants’ original treatment allocation in line with intention-to-treat principles, including all available data in all analyses, with no cases omitted.

### Primary Outcome Analysis

To evaluate the primary outcome, change in CGI-S scores will be analyzed using a cumulative link mixed model (CLMM) implemented in the ordinal package in R (R Project for Statistical Computing).^42^ The model will include a random intercept for participant, a dummy-coded site variable, a dummy-coded time variable (before treatment, immediately after treatment, and 3 months after treatment, with before treatment as the reference category), the treatment condition, and the interaction between the time variable and treatment. Coefficients from the CLMM represent the log odds of being classified in a higher CGI-S category, these will be converted to odds ratios.

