### Secondary Outcomes Analyses

For secondary outcomes, linear mixed-effects regression models, with the same predictors and covariates as the CLMM model will be used. Effect sizes will be estimated as Cohen d for mixed-effects models by dividing the unstandardized β coefficient for the time x treatment interaction by the baseline SD, with 95% bootstrap confidence intervals derived from 1000 simulations. Under the assumption that data are missing at random, mixed-effects regression analyses for repeated measures (including all assessment points), provide unbiased estimates and standard errors.^43^ This assumption indicates that, conditional on observed data, the probability of missingness depends only on observed variables and not on unobserved values.^44^ If >30% of the primary outcome data are missing at the primary end-point, we will conduct NMAR sensitivity analyses to assess the robustness of the results to departures from the MAR assumption. For CGI-I, the number of participants classified as responders will be presented. Treatment response is defined as a CGI-I rating of 1 (“very much improved”) or 2 (“much improved”).^15,45,46^ Differences between treatment groups in participant satisfaction and therapist time will be analyzed using independent samples t tests. To examine whether blinded assessors’ guesses of treatment allocation differ from chance, a t test will be conducted. All tests will be 2-sided, with statistical significance set at P < .05.

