### Long-term and distal outcomes data

Additional analyses of primary and secondary outcomes at 1-year and 5-year follow-up will assess whether treatment effects are sustained over the long term, using the same statistical analysis method applied at the primary endpoint. Data on distal outcomes will be obtained from Swedish national registries. This data will vary in type and distribution such as continuous (e.g., grade point average), binary (e.g., eligibility for higher education), count (e.g., number of health care contacts), and time-to-event (e.g., suicide), appropriate regression models will be fitted accordingly.

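### A participant random intercept alone forces one correlation on every pair of visits, so the standard errors are not assured: likely too small at 3 months, wrong in either direction at the primary endpoint

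*Protocol*

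**What the plan says.** Primary Outcome Analysis specifies a cumulative link mixed model (CLMM) for CGI-S: "The model will include a random intercept for participant, a dummy-coded site variable, a dummy-coded time variable". The time variable has three levels, "before treatment, immediately after treatment, and 3 months after treatment, with before treatment as the reference category". Treatment enters through "the treatment condition, and the interaction between the time variable and treatment", so each tested effect is a difference in change from baseline.

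Secondary Outcomes Analyses uses "linear mixed-effects regression models, with the same predictors and covariates as the CLMM model will be used". It adds that, under missing at random, "mixed-effects regression analyses for repeated measures (including all assessment points), provide unbiased estimates and standard errors", and sets the threshold: "All tests will be 2-sided, with statistical significance set at P < .05". Long-term and distal outcomes data treats 1 and 5 years by "using the same statistical analysis method applied at the primary endpoint".

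The simulation in Power analysis, Primary outcome, had two time points only: "a dummy-coded time variable (before treatment, after treatment". The Protocol states no further random effect, unstructured covariance, robust standard error or sensitivity analysis on the covariance.

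**The concern.** With two visits there is one correlation, and a random intercept can match it. With three there are three, and the random intercept makes them equal (on the latent scale for the CLMM). The model then builds the standard error of a change from baseline out of the average within-person variability. If baseline correlates less with a given follow-up than the average pair does, that standard error is too small; if it correlates more, too large.

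The Protocol's own hypotheses make unequal correlations plausible. Hypothesis 5.1 expects participants to differ in response and Hypothesis 6.1 expects effects to last. Response that varies between participants and persists is shared by the two follow-ups and absent at baseline.

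At stake are the error rate of the primary test, the hypotheses at 3 months, and the claim that missing at random is enough for valid standard errors.

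**Working it through.** **Inputs from the Protocol:** three visits; contrasts against baseline; two-sided 5%; 1:1 allocation; 350 evaluable of 388.

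**Assumed:** correlations by visit and CGI-S thresholds (neither is given); complete data; equal variances unless stated.

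**The plan's own figure.** 350 / 0.90 = 388.9, against the stated 388, so it reproduces. Two-visit CLMM simulations at N = 350 and odds ratio 2.2 gave 72–82% power, depending on thresholds and ICC. The stated power above 80% is attainable but cannot be confirmed without the pilot thresholds. A two-visit simulation cannot show the present problem.

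**Linear case.** For the change to follow-up k, the true variance is proportional to 1 − ρ₀ₖ, where ρ₀ₖ is its correlation with baseline. The random-intercept model uses 1 − ρ̄, with ρ̄ the mean over all pairs. Hence

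- ratio = model SE / true SE = √[(1 − ρ̄)/(1 − ρ₀ₖ)]
- true type I error = 2[1 − Φ(1.96 × ratio)]

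Example 0.4/0.4/0.7: ρ̄ = 1.5/3 = 0.5; ratio = √(0.5/0.6) = 0.913; 1.96 × 0.913 = 1.789; type I error 7.4%.

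| Baseline–POST / baseline–3M / POST–3M | ρ̄ | Ratio POST | Type I POST | Ratio 3M | Type I 3M |
|---|---|---|---|---|---|
| 0.5/0.5/0.5 | 0.500 | 1.000 | 5.0% | 1.000 | 5.0% |
| 0.4/0.4/0.6 | 0.467 | 0.943 | 6.5% | 0.943 | 6.5% |
| 0.3/0.3/0.6 | 0.400 | 0.926 | 7.0% | 0.926 | 7.0% |
| 0.4/0.4/0.7 | 0.500 | 0.913 | 7.4% | 0.913 | 7.4% |
| 0.3/0.3/0.7 | 0.433 | 0.900 | 7.8% | 0.900 | 7.8% |
| 0.5/0.4/0.6 | 0.500 | 1.000 | 5.0% | 0.913 | 7.4% |
| 0.53/0.37/0.37 (decay) | 0.423 | 1.108 | 3.0% | 0.957 | 6.1% |
| 0.53/0.37/0.53 (decay) | 0.477 | 1.055 | 3.9% | 0.911 | 7.4% |
| 0.5/0.25/0.5 (autoregressive) | 0.417 | 1.080 | 3.4% | 0.882 | 8.4% |
| 0.6/0.36/0.6 (autoregressive) | 0.520 | 1.095 | 3.2% | 0.866 | 9.0% |

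Unequal variances soften this: 0.4/0.4/0.6 with the baseline SD at 0.8 of the follow-up SD gives ratio 0.966 and 5.8%.

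The mechanism can be checked directly. Take intercept and residual variances of 1 and a persistent response variance d. Then ratio² = 2(1 + d/3)/(2 + d). For d = 0.25, 0.5 and 1.0 the type I error is 5.4%, 5.8% and 6.5%.

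If 1 and 5 years join the same model (an assumption), five visits with 0.4 to baseline and 0.6 among follow-ups give ratio 0.894 and 8.0%.

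**CLMM.** Null simulations, three visits, N = 350, 1,500 datasets each. Monte Carlo error is √(0.05 × 0.95/1500), about 0.6 points. Intercept variances were 2.19 and 4.93, which give latent ICC 2.19/(2.19 + 3.29) = 0.40 and 4.93/(4.93 + 3.29) = 0.60.

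| Latent correlation, baseline–follow-up v between follow-ups | Type I POST / 3M | Model SE / empirical SD, POST / 3M |
|---|---|---|
| 0.40 v 0.40 (control) | 5.3% / 5.5% | 1.00 / 0.97 |
| 0.60 v 0.60 (control) | 5.3% / 5.6% | 0.98 / 0.96 |
| 0.30 v 0.40 | 5.0% / 6.0% | 0.98 / 0.96 |
| 0.20 v 0.40 | 5.9% / 7.0% | 0.96 / 0.93 |
| 0.45 v 0.60 | 5.9% / 6.9% | 0.95 / 0.93 |
| 0.30 v 0.60 | 6.5% / 7.3% | 0.92 / 0.91 |

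**Attenuation.** With 0.30 v 0.60 and a true log-odds ratio of 0.79 (odds ratio 2.2), the random-intercept model averaged 0.62 at POST (e^0.62 = 1.86). A model with a correlated post-baseline effect averaged 0.78 (e^0.78 = 2.18). Each rests on 300 datasets.

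**After the fix, under the null.** The three-visit CLMM with that extra effect rejected in 4.0–4.3% at POST and 4.3–5.5% at 3 months (400 datasets per scenario). A random intercept fitted to baseline and POST only rejected in 4.0–4.6% (1,000 datasets per scenario).

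**The case against.** The strongest reply is that the direction at the primary endpoint is assumed. Baseline to POST is about 7 weeks and POST to 3 months about 13, so correlation that fades with time favours the baseline–POST pair and makes the primary test conservative. This stands. A reader might infer that the confirmatory test rejects too often as a matter of course; the documents give no correlations by visit and do not support that.

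Second, the effect on the primary model is small. The correctly specified controls reject in 5.3%, so the excess at POST is about 0.6–1.2 points in the clearer cases and absent in the mildest. This stands too. The 7.4% belongs to a continuous outcome and should not be quoted for CGI-S.

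Third, a reader might take the reference to all assessment points to mean that weekly scales enter with nine visits, where the distortion would be larger. That phrase sits inside the missing-data rationale, and the carried-over time variable has three levels. Weekly assessment is listed under Secondary endpoint, so the text is ambiguous. No conclusion should rest on nine visits unless weekly data are confirmed to enter these models.

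Fourth, the secondary models inherit predictors and covariates explicitly, but their random part is not restated. Their planned bootstrap intervals for Cohen d are of unstated type: resampling participants would resist the problem, a parametric bootstrap would not. So it is not established that every planned interval is too narrow.

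What the reply does not remove: the random intercept over three visits is stated for the primary outcome, and missing at random alone does not make the standard errors valid.

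**Conclusion.** The point holds in conditional form. The stated model ties all visit pairs to one correlation, and the sentence on unbiased standard errors leaves out a condition that it needs. At 3 months every unequal pattern tried in the linear case with equal variances gave too small a standard error, with type I error of about 6–8% and 9.0% in the steepest case. At the primary endpoint the linear error ran from 3.0% to 7.8%, with 5.0% at 0.5/0.4/0.6. For CGI-S, where follow-ups clearly correlate more with each other than with baseline, it is about 6–6.5% at POST and about 7% at 3 months, with possible attenuation of the odds ratio. All sizes rest on assumed correlations, and the CLMM figures also on assumed thresholds. The change is worth making because it is cheap and gives valid error rates whichever pattern occurs, not because the primary test is shown to be badly inflated.

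**What to change.** - **Continuous outcomes:** state an unstructured within-participant covariance over visits (a mixed model for repeated measures) with small-sample degrees of freedom.
- **CGI-S:** add to the CLMM a post-baseline participant random effect correlated with the intercept. Keep the time-by-treatment contrast and all randomised participants. Alternatively, fit baseline and POST only as a sensitivity analysis for the primary contrast.
- **Secondary Outcomes Analyses:** amend the sentence to say that valid standard errors also require a correctly specified covariance, and state whether weekly assessments enter these models.
- **1 and 5 years:** apply the same structure.

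Two other options are weaker. Participant-clustered standard errors would leave the attenuation in place. Using baseline CGI-S as a covariate would replace the contrast on which the trial was powered and drop participants without a follow-up rating, contrary to the commitment under Analysis of Baseline Characteristics to omit no cases.

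The cost is one or two more variance parameters, a convergence check with a named fallback, and somewhat different interval widths. Where the extra variance is large, the change on the log-odds scale is visible. In the 0.30 v 0.60 scenario with a true odds ratio of 2.2, the mean standard error at POST rose from 0.29 to 0.38 as the estimate rose from 0.62 to 0.78. Rejection went from 56% to 50% (300 datasets each, Monte Carlo error about 3 points), and the random-intercept figure comes from a test that exceeds its nominal level under the null. No new data or visits are needed.

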# Outcome measures

## Primary Outcome Measure

**Clinician rated clinical global symptom severity** will be measured with The Clinical Global Impressions-Severity (CGI-S).^19^The CGI-S is an ordinal scale ranging from 1 to 7, with higher scores indicating greater severity. CGI-S is administered by a blinded assessor before randomization and at immediately after treatment (primary endpoint), 3 months after treatment, and at 1 and 5 years follow.

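### The mixed models estimate a baseline treatment difference that randomisation makes zero: the test is valid, but it gives up power that a common-baseline model would recover

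*Protocol*

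**What the plan says.** Under Primary Outcome Analysis, the Protocol specifies a cumulative link mixed model (CLMM) for CGI-S with a random intercept, site, three time points "with before treatment as the reference category), the treatment condition, and the interaction between the time variable and treatment". Under Primary Outcome Measure, "CGI-S is administered by a blinded assessor before randomization", and under Randomization, "Eligible participants will be randomly assigned (1:1) to either the POET intervention or the Supportive Treatment condition".

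Under Secondary Outcomes Analyses, "linear mixed-effects regression models, with the same predictors and covariates as the CLMM model will be used", and Cohen's d is obtained by "dividing the unstandardized β coefficient for the time x treatment interaction by the baseline SD". The Power analysis section sizes the trial on the same interaction: 350 participants for more than 80% power at an odds ratio of 2.2, raised to 388 for attrition. For continuous outcomes, with 388 participants, 10% attrition and ICC 0.5, "the study has >80% power to detect a difference 0.30" on the Cohen's d scale.

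Nowhere does the Protocol constrain the baseline means to be equal or adjust for baseline as a covariate.

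**The concern.** With baseline as the reference time, the treatment coefficient is a freely estimated arm difference at baseline, and the interaction is the arm difference after treatment minus the arm difference at baseline. Since the true baseline difference is zero by design, estimating it only adds its sampling error to the treatment effect. For two waves with equal variance and correlation r, the variance of the treatment effect is proportional to 2(1 - r) under this model, and to 1 - r² when the arms share a baseline. The second is smaller for every r below 1.

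At stake is precision that the trial has already paid for, on its primary test and on the secondary scales that have a baseline value.

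**Working it through.** **1. Continuous outcomes: reproduce the stated power.** Inputs from the power section for secondary continuous outcomes: 194 per arm, 10% attrition (0.9 × 194 = 174.6 per arm with both values), r = ICC = 0.5, d = 0.30, two-sided 5%.

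- Difference in change: variance factor 2(1 - 0.5) = 1.00. SE = √(2 × 1.00 / 174.6) = 0.107. Power = Φ(0.30/0.107 - 1.96) = 80.0%.
- If the dropouts' baseline values also enter by maximum likelihood: SE 0.1057, power 81.0%.

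This agrees with the stated figure of more than 80%. At r = 0.5 the factor of 1.00 is also that of a comparison of post-treatment values alone, so among completers the planned contrast gains nothing from the baseline.

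**2. The same inputs with a common baseline.** Variance factor 1 - 0.25 = 0.75. SE = √(2 × 0.75 / 174.6) = 0.0927. Power = 89.9%. The difference detectable with 80% power falls from 0.296 (maximum likelihood) to 0.260. To match this precision, the planned model would need about 388 × (0.1057/0.0927)² ≈ 504 randomised, or 388 × 1.00/0.75 ≈ 517 on the completer calculation.

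**3. Dependence on the correlation** (d = 0.30, 174.6 per arm with both values):

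| r | Planned, completers | Planned, with dropouts' baselines | Common baseline | Gain (points) |
|---|---|---|---|---|
| 0.4 | 72.5% | 73.8% | 86.4% | 13-14 |
| 0.5 | 80.0% | 81.0% | 89.9% | 9-10 |
| 0.6 | 88.0% | 88.6% | 93.9% | 5-6 |
| 0.7 | 95.1% | 95.4% | 97.5% | about 2 |

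The Protocol gives only ICC 0.5 for these outcomes. The other rows show sensitivity.

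**4. CGI-S.** Inputs from the power section for the primary outcome: 350 participants, odds ratio 2.2, random-intercept variance 1.48 or 2.22. The pilot thresholds and time effect are not given, so four baseline CGI-S distributions and time effects from 0 to -2 log-odds were assumed. Power was computed from the expected information of the random-intercept cumulative-logit model, with and without a baseline treatment term, and checked with 700 simulated datasets under one assumed setting.

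| Variance | Planned | Common baseline | Simulation: planned to common |
|---|---|---|---|
| 1.48 | 73-81% | 88-94% | 76.9% to 91.9% |
| 2.22 | 72-80% | 85-92% | 76.7% to 89.4% |

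The gain is about 11-16 points by information, and 15.0 and 12.7 points by simulation. A planned-model power near 77% from 700 datasets has a Monte Carlo SE of √(0.77 × 0.23/700) = 1.6 points.

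**5. Two checks on the CGI-S result.**

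- Adding the 3-month row, which the analysis model has and the power model lacks, changes power by about 0.5 point under either model, so it does not recover the loss.
- On the logit scale, variances 1.48 and 2.22 correspond to latent ICCs of 1.48/(1.48 + 3.29) = 0.31 and 2.22/(2.22 + 3.29) = 0.40. At a latent ICC of 0.6 (variance 4.935, outside the Protocol's range) the gain is about 8-11 points.

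**The case against.** The strongest reply is that nothing is wrong with the planned test. The interaction is a valid estimate under randomisation, it answers the hypothesis about greater reductions, and it is what both power calculations used. The stated secondary power reproduces under it. All of that stands. The loss is relative to a better model and is not a failure to deliver the planned power.

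A reader might infer three stronger things that the document does not support:

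- **That the trial falls short of its stated primary power.** The information calculation gives 72-77% under concentrated CGI-S distributions, but 80-81% when seven categories are used evenly. Without the pilot thresholds, the stated figure can be neither confirmed nor refuted.
- **That a fixed gain applies to every outcome.** The secondary scales will not share one correlation, and the gain shrinks as the correlation rises. In addition, Table 2 shows no baseline for CGI-I, DSHI-Y or CSQ, and the Protocol analyses satisfaction and therapist time with t tests.
- **That adjusting for baseline as a covariate is the same model.** It is not in a cumulative-logit model. Odds ratios are non-collapsible, so the covariate form estimates an odds ratio conditional on baseline. It also drops participants who have no post-baseline rating, which sits badly with the Protocol's commitment to omit no cases.

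A separate statistical analysis plan was not available. If it already fixes a common baseline, the Protocol needs only to be aligned with it.

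**Conclusion.** The point holds as one of efficiency, with no bias and no inflation of type I error. The Protocol spends information on a baseline difference that is known to be zero in expectation.

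The continuous-outcome gain, from 80-81% to 90%, rests on the Protocol's own inputs, with equal variances at both waves and the ICC taken as the correlation between them. The CGI-S gain of 11-16 points also depends on the assumed category distributions and time effects, and on proportional odds. Its direction is the same in every setting tried, but its exact size cannot be fixed from the document. The change is worth making because the stated margin above 80% is thin and no further participants are needed.

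**What to change.** By amendment before unblinding, constrain both arms to a common baseline in the CLMM and in the linear mixed models for outcomes with a baseline value. Keep the random intercept, site and time, with separate treatment terms at the post-treatment and 3-month assessments where the outcome is measured. Participants with only a baseline value stay in the analysis.

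Specify the coding. In R, `~ time + time:treat` gives the same number of columns as `~ time*treat`, including one for treatment at baseline, so deleting the main effect from the formula can refit the same model. Use explicit 0/1 indicators for treatment at each post-baseline assessment, set to zero for everyone at baseline. Define Cohen's d from these coefficients.

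Modelling only the post-baseline rows with the baseline score as covariate is an alternative, with the different odds ratio and the loss of participants noted above. Its own advantage is that it avoids fitting common thresholds to a baseline that inclusion restricts to CGI-S of 2 or higher. If it is chosen, the estimand should be stated accordingly.

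The cost is an amendment reported to the ethics authority and the trial registry, as the Ethics section requires, and slightly more coding.
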